### Clinical data

2.2

We will collect demographic information, vascular risk factors, and blood test results. Vascular risk factors include smoking, hypertension, diabetes, hyperlipidemia, coronary artery disease and previous ischemic stroke. Blood test data include low-density lipoprotein (LDL), high-density lipoprotein (HDL), total cholesterol, triglyceride, urea nitrogen, serum creatinine, aspartate transaminase (AST) or alanine transaminase (ALT), C-reactive protein (CRP), erythrocyte sedimentation rate (ESR), interleukin 6 (IL6), procalcitonin, glycosylated hemoglobin, D-dimmer and fibrinogen (FIB), and blood routine examination.

### HR-vwMRI protocol

2.3

All images were performed using a 3.0 T magnetic resonance (MR) (Magnetom Verio or Skyra, Siemens, Erlangen, Germany) equipped with a 32-channel or a 20-channel head-matrix coil. The detailed protocol has been described before (7). Briefly, this HR-vwMRI includes sequences as below: three-dimensional time-of-flight MR angiography (3D TOF-MRA), axial DWI (diffusion weighted imaging), 3D T1-weighted SPACE (sampling perfection with application optimized contrast using different angle evolutions), two-dimensional black blood (2D-BB) T2WI, dynamic susceptibility contrast-perfusion weighted imaging (DSC-PWI) conducted with a gradient echo planar sequence using of a bolus of 0.1 mmol/kg contrast agent (gadodiamide, GE Healthcare, Cork, Ireland). In addition, contrast-enhanced 3D T1-weighted SPACE will be acquired with an around 5-min delay time after contrast administration. It takes approximately 25 min to complete all sequences above.

### Image analysis

2.4

Two neuroradiologists will independently analyze HR-MRI images on commercially available software (Carestream Vue PACS v12.1, Carestream Health), and they were blinded to all clinical information. A senior neuroradiologist will give a further review on images with uncertainty grading to reach a consensus.

The characteristics of the plaque, such as stenosis degree, enhancement, the presence of T1 hyperintensity, remodeling index, plaque burden, and the distribution of the plaque, will be assessed. The detailed imaging analysis on HR-vwMRI has been described before (7). Briefly: (1) degree of stenosis = (1 − D_plaque_/D_reference_) × 100%, where D_plaque_ means the diameter of the stenotic artery at the most stenotic site, and D_reference_ is the diameter of the normal artery proximal to the plaque; (2) grading of plaque enhancement: grade 0 means enhancement is similar to or less than that of normal-appearing intracranial arterial walls in the same subject; grade 1, enhancement is greater than that of grade 0 but less than that of the pituitary infundibulum; and grade 2, enhancement is similar to or greater than that of the infundibulum (8); (3) plaque enhancement ratio (ER): neuroradiologists will draw circular region of interest (ROI) within the plaque on pre-contrast and post-contrast T1-weighted SPACE images, respectively. The mean signal intensity (SI) of plaques will be acquired. ER = (SI_post_ − SI_pre_)/SI_pre_ × 100% (9); (4) remodeling index (RI): the outer wall area (OWA) is manually contoured at the most stenotic site (OWA_plaque_) and the reference site (OWA_reference_) on T1-weighted SPACE. RI = OWA_plaque_/OWA_reference_ × 100%. Arterial remodeling is classified as positive if RI >1.05, intermediate if 0.95 ≤ RI ≤ 1.05, and negative if RI <0.95 (10); (5) plaque burden (PB): lumen area (LA) is manually contoured at the most stenotic site (LA_plaque_) on T1-weighted SPACE. PB = (1 − LA_plaque_/OWA_plauqe_) × 100% (11, 12); (6) presence of T1 hyperintensity: the brightest spot of the plaque whose SI is >150% of that of the reference vessel wall on pre-contrast T1 image (13); (7) plaque distribution: a concentric plaque is defined if the wall involvement is at least 75%, and the minimum wall thickness is bigger than 50% of the maximum wall thickness.

For patients experiencing an acute ischemic stroke within the middle cerebral artery (MCA) territory, infarct patterns on DWI will be categorized into four types: internal borderzone, cortical borderzone, core MCA and perforator (14). For infarction lesion that crossed these territories, the territory which is predominantly involved is chosen. DSC-PWI is derived through the application of the singular value decomposition deconvolution technique, facilitated by the software NeuBrainCARE (v1.1.10). The arterial input function is determined automatically, taken from the MCA on the opposite side. Hypoperfusion volume is automatically calculated using time to maximum (T_max_) with time thresholds of >4 s and >6 s, respectively.

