### Study design

2.1

This is a prospective, randomized, open-label, and blinded endpoint assessment study. We will recruit 80 patients who have recently suffered a stroke/transient ischemic attack (TIA) due to ICAS. The inclusion and exclusion criteria are shown in Tables 1, 2, respectively. Patients will be allocated in a 1:1 ratio to the evolocumab plus statin treatment arm or the statin alone treatment arm. Evolocumab (150 mg) will be injected subcutaneously every 2 weeks for 12 months. Both arms will receive statins for 12 months, including atorvastatin 20–80 mg or rosuvastatin 10–20 mg. According to current guideline and the standards in SAMMPRIS study, optimal medical management with aggressive control of the risk factors will be provided to all patients, such as proper application of antiplatelet, antihypertensive, and antidiabetic drugs. HR-vwMRI will be performed at baseline and at 6th and 12th month after recruitment. Blood test will be conducted at baseline and at 1st, 3rd, 6th, and 12th month after recruitment. National Institute of Health Stroke Scale (NIHSS), modified Rankin Scale (mRS), Barthel index, Mini-Mental State Examination (MMSE), and Montreal Cognitive Assessment (MoCA) will be evaluated at baseline and at 3rd, 6th, and 12th month post-recruitment. This study was approved by the ethics board of the first affiliated hospital of Nanjing Medical University. Written informed consents will be obtained. The flow chart of this study is shown in Figure 1.

**Table 1 tab1:** Inclusion criteria.

1. Age ≥30 years and ≤75 years
2. TIA or acute ischemic stroke that occurred within 6 weeks prior to randomization
3. Modified Rankin score of ≤4
4. TIA or acute ischemic stroke attributed to a 50 to 99% stenosis of a major intracranial artery [internal carotid artery (ICA), vertebral artery (VA), basilar artery (BA) and the M1 segment of middle cerebral artery (MCA)]. The diagnostic evaluation for ICAS at each site is confirmed by the local investigator, using high resolution MR
5. To increase the likelihood that the symptomatic intracranial stenosis is atherosclerotic, patients aged 30–49 years are required to meet at least one additional criteria (i–vi) below:
o Insulin dependent diabetes for at least 15 years

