o At least 2 of the following atherosclerotic risk factors: hypertension [blood pressure (BP) ≥140/90 or on antihypertensive therapy]; dyslipidemia [LDL ≥130 mg/dL or high density lipoprotein (HDL) <40 mg/dL or fasting triglycerides ≥150 mg/dL or on lipid lowering therapy]; smoking; non-insulin dependent diabetes or insulin dependent diabetes of less than 15 years duration; family history of any of the following: myocardial infarction, coronary artery bypass, coronary angioplasty or stenting, stroke, carotid endarterectomy or stenting, peripheral vascular surgery in parent or sibling who was <55 years of age for men or <65 for women at the time of the event
o History of any of the following: myocardial infarction, coronary artery bypass, coronary angioplasty or stenting, carotid endarterectomy or stenting, or peripheral vascular surgery for atherosclerotic disease
o Any stenosis of an extracranial carotid or vertebral artery, another intracranial artery, subclavian artery, coronary artery, iliac or femoral artery, other lower or upper extremity artery, mesenteric artery, or renal artery that was documented by non-invasive vascular imaging or catheter angiography and is considered atherosclerotic
o Aortic arch atheroma documented by non-invasive vascular imaging or catheter angiography
o Any aortic aneurysm documented by non-invasive vascular imaging or catheter angiography that is considered atherosclerotic
6. Patient agrees with follow-up visits and is available by phone
7. Patient understands the purpose and requirements of the study, can make him/herself understood, and has signed informed consent

**Table 2 tab2:** Exclusion criteria.

1. Previous treatment of target intracranial lesion with a stent, angioplasty, or other mechanical devices (e.g., mechanical thrombectomy, coil embolization)
2. Plan to perform angioplasty, stenting, coiling, thrombectomy, endarterectomy or aneurysmal coil embolization for target vessels/plaques. In case that patients who receive surgeries during follow-up, they will still be followed up for 1 year
3. Intracranial tumor (except meningioma) or any intracranial vascular malformation
4. History of any intracranial hemorrhage (parenchymal, subarachnoid, subdural, epidural)

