### Study outcomes

3.1

Primary endpoints:

1) Changes in plaque enhancement.

A reduction of ≥ 1 grading in plaque enhancement after 12 months’ treatment was regarded as relief of plaque enhancement. For example, a patient’s plaque enhancement reduces to grade 1 or even 0 after 12 months’ treatment, compared to grade 2 at the time of enrollment.

2) Changes in degree of stenosis.3) Changes in plaque enhancement ratio.4) Changes in plaque burden.5) Changes in hypoperfusion volume.6) T1 hyperintensity.

We define three types of T1 hyperintensity changes at 12 month after recruitment: type A, no changes before and after treatment; type B, disappearance of T1 heperintensity; type C, new T1 hyperintensity.

7) Changes in remodeling index (RI) of the plaque.

Secondary endpoints:

1) Recurrent stroke (ischemic or hemorrhagic) or death during follow-up.2) Changes in LDL-cholesterol levels.3) Changes in NIHSS/Barthel index/mRS score.4) Changes in MoCA/MMSE score.

All changes above before and after treatment in each arm will be calculated and compared between arms.

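### The arterial input rule for hypoperfusion volume, a primary endpoint, cannot be applied to basilar lesions and is unreliable when the opposite MCA is itself stenosed

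*Protocol article*

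**What the plan says.** Section 3.1 (Study outcomes) places "5) Changes in hypoperfusion volume" fifth among seven primary endpoints. It is to be compared between arms as a within-patient change, and nothing limits it to particular arteries.

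Section 2.4 (Image analysis) says how the volume is obtained. On the input: "The arterial input function is determined automatically, taken from the MCA on the opposite side". On the volume: "Hypoperfusion volume is automatically calculated using time to maximum (T_max_) with time thresholds of >4 s and >6 s, respectively". No alternative input is given.

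Table 1, criterion 4, lists the arteries in which the symptomatic stenosis may lie: "internal carotid artery (ICA), vertebral artery (VA), basilar artery (BA) and the M1 segment of middle cerebral artery (MCA"). Criterion 5, which supports an atherosclerotic cause at ages 30–49, accepts among other things "Any stenosis of an extracranial carotid or vertebral artery, another intracranial artery". Table 2 excludes intracranial stenosis from non-atherosclerotic causes, but it does not exclude atherosclerotic stenosis of a second intracranial artery.

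On timing, section 2.1 states: "HR-vwMRI will be performed at baseline and at 6th and 12th month after recruitment".

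**The concern.** An input rule defined by the opposite side assumes that the lesion has a side and that the opposite MCA is a sound reference. The eligibility criteria guarantee neither. For a basilar lesion the rule does not say which artery to use. For a patient whose opposite MCA is also narrowed, the rule directs the software to an input that may itself arrive late. In both cases the recorded volume depends partly on something other than the target lesion, and the endpoint is a change over 12 months in a trial of only 40 patients per arm.

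**Working it through.** The plan gives no figure to reproduce: the article states 80 patients without an effect size, SD or power. The check sets the rule against the population and then illustrates the cost.

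**Rule against eligible target artery**

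| Target artery (Table 1, criterion 4) | Has a side? | Is the opposite MCA defined? |
|---|---|---|
| ICA | yes | yes |
| M1 of the MCA | yes | yes |
| Vertebral | yes (paired) | yes |
| Basilar | no (single, midline) | no |

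Only the basilar row fails outright. The endpoint in section 3.1 still covers these patients.

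**Effect of a delayed input**

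Tmax comes from deconvolution against the arterial input, so to a first approximation it measures tissue delay relative to that input. Suppose a stenosed opposite MCA delivers its signal δ seconds late:

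- measured Tmax = true Tmax − δ;
- measured volume above 4 s = tissue with true Tmax above 4 + δ;
- measured volume above 6 s = tissue with true Tmax above 6 + δ.

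With δ > 0, both volumes are understated.

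Write V(t; c) for the true volume at visit t with delay above c seconds. For the 4 s threshold, the recorded 12-month change is V(12; 4 + δ₁₂) − V(0; 4 + δ₀).

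- If δ₀ = δ₁₂, part of the error cancels, but the change is still measured at a higher threshold than the one stated.
- If δ₀ ≠ δ₁₂ because disease in the opposite MCA has progressed or regressed, the recorded volume changes even when the target lesion and its territory do not.

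**Illustration of lost precision**

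Inputs: 40 per arm (80 patients, 1:1, section 2.1); α = 0.05 (section 3.3; two-sided assumed); power 80% (assumed); share of patients with no usable value 0–30% (assumed, as the documents give none).

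Formula: detectable difference in SD units = (1.960 + 0.842) × √(2/n), with n per arm.

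| Share unusable (assumed) | n per arm | Detectable difference (80% power) | Power for a 0.6265 SD effect |
|---|---|---|---|
| 0% | 40 | 0.63 SD | 80.0% |
| 10% | 36 | 0.66 SD | 75.7% |
| 20% | 32 | 0.70 SD | 70.7% |
| 30% | 28 | 0.75 SD | 65.0% |

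The table treats affected patients as lost. If their values are kept but mismeasured, precision also falls, by an amount the documents do not allow one to calculate.

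**The case against.** **This is a condensed article.** Sections 2.3 and 2.4 refer to an earlier description of the imaging method, and fallback arteries or quality checks may be set out in a fuller document. That would answer a complaint about silence. Here the article states a rule, and as stated it does not fit an artery the trial enrols.

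**The rule may be meant only for MCA-territory strokes.** The preceding sentences in section 2.4, on infarct patterns, are limited to those patients. The perfusion sentences do not repeat the limit, and neither does the endpoint. If the limit was intended, it has to appear in both places.

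**A diseased opposite MCA may be rare.** Criterion 5 applies only at ages 30–49, offers several alternatives and does not name the opposite MCA. It shows that such disease is permitted, not how common it is. This stands: the frequency is unknown.

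**The basilar gap may be small in practice.** Neither MCA is then the target artery, and the open question is which one to use. This too stands, and it is why a short clarification is enough.

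A reader might infer more than the documents support:

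- *That the input can switch sides between visits.* For a lateralised lesion, the side of the lesion fixes the artery. Automatic selection could vary the site within it, but the article does not address this and it is not a finding in itself.
- *That every posterior-circulation patient falls outside the rule.* Vertebral lesions have a side, so the rule is formally defined for them.
- *That two Tmax thresholds add an independent primary test.* The volume above 6 s lies within the volume above 4 s, so the two results are strongly dependent, and choosing the lead threshold is commonly left to the statistical analysis plan.
- *That patient safety is at issue.* The matter is reliability of measurement only.

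**Conclusion.** The point holds as a mismatch between a stated measurement rule and the stated population. For basilar lesions the rule cannot be applied as written. For patients with a stenosed opposite MCA it can be applied but tends to understate hypoperfusion volume, and it lets change in a non-target artery enter the endpoint.

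Selection of the input and calculation of the volume are automatic, and the rule does not depend on arm. The expected result is therefore measurement error and reduced precision on one of seven primary endpoints. One might argue that a systemic lipid-lowering drug could alter the opposite MCA differently in the two arms and so bias the comparison. That is possible in principle, but nothing in the documents demonstrates it.

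The size cannot be fixed, because neither the share of basilar lesions nor the share with a diseased opposite MCA is given. The 0.63 to 0.75 SD range rests on assumed losses of 0–30% and is an illustration, not an estimate. The conclusion about delayed input rests on Tmax being measured relative to that input.

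**What to change.** Amend section 2.4 as follows:

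1. Take the arterial input from an MCA without significant stenosis on the baseline MRA, and define what counts as significant. The time-of-flight MRA is already part of the scan protocol in section 2.3.
2. For lateralised lesions, keep the opposite MCA as the default.
3. For basilar lesions, and where the opposite MCA is diseased, use a named non-stenosed MCA chosen at baseline.
4. Use the same artery at 6 and 12 months, and record any scan on which it has become diseased.

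The cost is a few sentences and a brief check of the automatic input at each scan. A few patients with no suitable artery may lack this endpoint; their number should be reported. Limiting the endpoint to lateralised anterior-circulation lesions would also be coherent, but it would exclude more patients and lose precision in the way the table shows.

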### Neurological function and cognitive function

2.5

At baseline and then after 3, 6, and 12 months, we will evaluate NIHSS for neurological deficits, Barthel index for activities of daily living, mRS for the degree of disability in daily activities, MMSE, and MoCA for cognitive functions.

## Results

3

### Study outcomes

3.1

Primary endpoints:

1) Changes in plaque enhancement.

A reduction of ≥ 1 grading in plaque enhancement after 12 months’ treatment was regarded as relief of plaque enhancement. For example, a patient’s plaque enhancement reduces to grade 1 or even 0 after 12 months’ treatment, compared to grade 2 at the time of enrollment.

2) Changes in degree of stenosis.3) Changes in plaque enhancement ratio.4) Changes in plaque burden.5) Changes in hypoperfusion volume.6) T1 hyperintensity.

We define three types of T1 hyperintensity changes at 12 month after recruitment: type A, no changes before and after treatment; type B, disappearance of T1 heperintensity; type C, new T1 hyperintensity.

7) Changes in remodeling index (RI) of the plaque.

Secondary endpoints:

1) Recurrent stroke (ischemic or hemorrhagic) or death during follow-up.2) Changes in LDL-cholesterol levels.3) Changes in NIHSS/Barthel index/mRS score.4) Changes in MoCA/MMSE score.

All changes above before and after treatment in each arm will be calculated and compared between arms.

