### Statistical analysis

3.3

Appropriate statistical methods, such as Fisher’s exact test or Pearson’s chi-squared test, will be employed for the analysis of categorical data. Continuous variables will be compared by an independent samples Student’s *t*-test or Mann–Whitney *U*-test, as appropriate. We will present the cumulative incidence of stroke or mortality over a 12-month maximum follow-up period using Kaplan–Meier analysis, and we will determine the hazard ratios along with their 95% confidence intervals through the application of Cox proportional hazards modeling and the log-rank test to assess the efficacy of the treatment. Statistical significance is defined as a *p* value of < 0.05.

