## Discussion

4

This prospective, randomized, open-label, blinded end-point study seeks to investigate the impact of evolocumab plus statin on ICAS. We hypothesize that evolocumab added to statin therapy (EAST) will demonstrate greater efficacy in stabilizing intracranial plaques, as assessed by HR-vwMRI, when compared to the arm of statin alone without evolocumab. Multiple plaque features (enhancement, plaque burden, degree of stenosis, remodeling index, T1 hyperintensity) and hemodynamic markers (hypoperfusion volume defined by T_max_) will be compared between patients with and without evolocumab. Additionally, we will also document and compare neurological function, cognitive performance, blood parameters levels, and the incidence of recurrent stroke between arms.

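### Seven primary endpoints share one p < 0.05 with no ordering, adjustment or success rule; if any one suffices, the chance of a false-positive primary result could reach about 30%

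*Protocol article*

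**What the plan says.** Section 3.1 (Study outcomes) has a numbered list of primary endpoints. It opens with "1) Changes in plaque enhancement", continues with "2) Changes in degree of stenosis.3) Changes in plaque enhancement ratio.4) Changes in plaque burden.5) Changes in hypoperfusion volume.6) T1 hyperintensity" and closes with "7) Changes in remodeling index (RI) of the plaque", so there are seven. The section then commits to testing every one of them: "All changes above before and after treatment in each arm will be calculated and compared between arms".

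Section 3.3 (Statistical analysis) names the tests for categorical and continuous data and gives a single decision threshold: "Statistical significance is defined as a *p* value of < 0.05". It states no order among the primary endpoints, no division of the 5%, no adjusted p-values and no rule for how many endpoints must be positive.

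Two other places affect the number of primary tests:

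- The abstract places the primary outcome at both month 6 and month 12. Section 3.1 ties only relief of enhancement and the T1 hyperintensity categories to month 12, and gives no time point for the other five.
- Section 2.4 (Image analysis) calculates hypoperfusion volume from Tmax "with time thresholds of >4 s and >6 s, respectively", and does not say which threshold defines the primary endpoint.

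**The concern.** The trial asks one question: does adding evolocumab to a statin stabilise intracranial plaque? The article offers seven measurements that could answer it and does not say how they combine. A reader of the results could take one nominally significant feature out of seven as a positive primary finding, and nothing in the text would contradict that. The 5% would then describe each test, not the conclusion.

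The reverse problem also arises. If enhancement improves while stenosis worsens, the article gives no agreed way to read the result.

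**Working it through.** The article states no familywise error rate and no power calculation, so there is no figure of its own to reproduce.

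**Inputs**

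- Number of primary endpoints: 7 (section 3.1).
- Threshold per test: 0.05 (section 3.3). Sidedness is not stated; two-sided is assumed.
- Correlation between the test statistics: not given. A common value ρ from 0 to 0.9 is assumed.
- Sample size: 80 patients allocated 1:1 (section 2.1), hence 40 per arm with no dropout.
- Decision rule examined: any one significant endpoint counts as success. This is a reading, not a stated rule.

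**Step 1. Independent tests**

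1 − (1 − 0.05)^7 = 1 − 0.698 = 0.302.

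For jointly normal statistics and two-sided tests this is also the ceiling, by Šidák's inequality, because correlation can only lower it. The Bonferroni bound under any dependence is 7 × 0.05 = 0.35.

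**Step 2. Correlated tests**

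Write each statistic as Z_i = √ρ·T + √(1−ρ)·E_i, with T and E_i independent standard normal. Then

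FWER = 1 − ∫ φ(t) · [Φ((1.96 − √ρ·t)/√(1−ρ)) − Φ((−1.96 − √ρ·t)/√(1−ρ))]^7 dt.

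| Assumed ρ | Chance of at least one false positive, 7 tests |
|---|---|
| 0 | 30.2% |
| 0.2 | 28.7% |
| 0.4 | 25.2% |
| 0.5 | 23.0% |
| 0.6 | 20.5% |
| 0.7 | 17.8% |
| 0.8 | 14.9% |
| 0.9 | 11.4% |

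An uneven pattern was also simulated: correlation 0.7 between enhancement grade and enhancement ratio and between stenosis and plaque burden, and 0.2 elsewhere. It gives 26.8%.

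**Step 3. Effect of Fisher's exact test**

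Two of the seven endpoints are categorical, and exact tests on them may have true size below 0.05. If that size is 0.02 to 0.04 and the tests are independent, 1 − 0.95^5 × (1 − a)^2 gives 25.7% at a = 0.02 and 28.7% at a = 0.04. The inflation changes little.

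**Step 4. More time points or thresholds**

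Section 3.1 fixes month 12 for two endpoints. Suppose the other five were tested at both months, with hypoperfusion volume at both thresholds. The most the text allows is then 2 + (4 × 2) + (2 × 2) = 14 tests. Fourteen tests give 1 − 0.95^14 = 51.2% if independent, 34.8% at ρ = 0.5 and 24.9% at ρ = 0.7. This shows direction only, since the article does not say that all of these are primary tests.

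**Step 5. What control would cost**

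The strictest Holm step for seven endpoints is 0.05/7 = 0.00714. Using that threshold for all seven (Bonferroni) holds the familywise error at 4.9% if independent and 3.2% at ρ = 0.7.

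The standardised difference detectable with 80% power is (z_{1−α/2} + 0.842) × √(2/40):

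- α = 0.05: (1.960 + 0.842) × 0.2236 = 0.63 SD.
- α = 0.00714: (2.690 + 0.842) × 0.2236 = 0.79 SD.

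Power for a true difference of 0.63 SD falls from 80% to 54% at the stricter threshold.

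**The case against.** **The analysis plan is not shown.** An article may leave multiplicity to the full protocol or the SAP, and section 3.3 is one condensed paragraph that does not exclude a correction. So it cannot be said that the trial has no adjustment anywhere. What stands is that the article does more than stay silent: it fixes seven primaries and one unqualified threshold, and that pairing is poorly specified as published.

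**The any-one-suffices rule is not written.** A reader might infer that a single significant endpoint is the stated success criterion. No section says so, and the error figures hold only under that reading. A reader might equally call the endpoints co-primary in the strict sense that all seven must succeed, in which case the false-positive rate would not exceed 5%. The article does not use that word or state that rule either.

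**The correlation is assumed.** Section 2.4 shows shared inputs. Enhancement grade and enhancement ratio measure one feature, plaque burden and remodeling index both use the outer wall area at the plaque, and stenosis and plaque burden both depend on the lumen at the narrowest site. Full independence is therefore a ceiling. Nor is 18% a floor, since a uniform correlation of 0.8–0.9 gives 11–15%. That is still two to three times 5%.

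**Larger test counts are tempting.** A reader might count eight tests because of the two Tmax thresholds, or sixteen by doubling that for two time points, which would give 56% if independent. The eighth test is an inference: section 2.4 says both volumes are calculated, not that both are tested as primary. The count of sixteen conflicts with section 3.1, which sets month 12 for two endpoints.

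**The study is small and urges caution.** Section 5 advises care because of the sample size and the single center. This lowers the stakes somewhat, but it does not address multiplicity, and the article does not call the primary analysis exploratory.

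**Conclusion.** The point holds as a defect in what the article fixes: seven primary endpoints, one 0.05 threshold, and no order or success rule. If any one significant endpoint is taken to support plaque stabilisation, the familywise error lies between about 11% and 30% over assumed common correlations of 0.9 down to 0, against a nominal 5%. The middle of that range is 23% at 0.5 and 18% at 0.7. Primary testing at both months or at both Tmax thresholds would add to this.

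The size rests on two assumptions that the article does not supply: the any-one-suffices reading and the correlation. The missing ordering and success rule depend on neither.

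**What to change.** Settle the following in the protocol and SAP before any between-arm comparison, including any made at the interim analyses mentioned in section 3.2.

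1. Name one primary endpoint at one time point. The choice is the sponsor's. Month-12 enhancement is a candidate because it is listed first and already has a responder definition. However, plaques at grade 0 at baseline cannot drop a grade, and Table 1 does not require enhancement at entry, so the handling of such patients would need stating.
2. Make the other six endpoints secondary and test them in a stated fixed order or with Holm.
3. Name one Tmax threshold for inference on hypoperfusion volume, and report the other descriptively.

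Alternatively, keep all seven as primary, test them with Holm at a familywise 5%, and state that the claim rests on the adjusted p-values.

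Neither route needs new data. With one primary endpoint, the full 5% and the corresponding power are kept for it, but some nominally significant features become supportive only. Keeping seven costs more power: with 40 per arm and no dropout, the strictest Holm step raises the detectable difference from about 0.63 to 0.79 SD, and dropout would raise both figures.

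### T1-hyperintensity endpoint: type A pools never-present with persistently present, and comparing the three types without baseline status costs direction and power, though it does not inflate type I error

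*Protocol article*

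**What the plan says.** Section 2.4 (Image analysis) defines T1 hyperintensity by a threshold: "the brightest spot of the plaque whose SI is >150% of that of the reference vessel wall on pre-contrast T1 image". The sign is therefore present or absent.

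Section 3.1 (Study outcomes) lists it as the sixth of seven primary endpoints. It states "We define three types of T1 hyperintensity changes at 12 month after recruitment" and gives them as "type A, no changes before and after treatment; type B, disappearance of T1 heperintensity; type C, new T1 hyperintensity". The section closes with "All changes above before and after treatment in each arm will be calculated and compared between arms".

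Section 3.3 (Statistical analysis) offers Fisher's exact and Pearson's chi-squared tests as examples of methods that "will be employed for the analysis of categorical data", with significance at p < 0.05. It mentions neither a denominator restricted to patients at risk nor baseline status.

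Section 2.1 (Study design) plans 80 patients: "Patients will be allocated in a 1:1 ratio to the evolocumab plus statin treatment arm or the statin alone treatment arm". Entry depends on a 50 to 99% stenosis. T1 hyperintensity at baseline is not an entry criterion, so patients with and without it can enrol.

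**The concern.** The trial asks whether evolocumab stabilises plaque. For that question, a plaque that never showed the sign and one that still shows it after a year are opposite outcomes. Type A gives them the same label, so a large type A share cannot be read as good or bad.

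The other two types have different populations at risk. Only baseline-positive patients can be type B, and only baseline-negative patients can be type C. A general test of A/B/C by arm then has three weaknesses:

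- It treats more disappearance and more new onset alike, as a departure from equality with no direction.
- It counts disappearance over many patients in whom disappearance was impossible.
- It lets a chance difference in baseline prevalence show up as a difference in types B and C.

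With about 40 patients per arm, the trial has little power to give away.

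**Working it through.** **Inputs from the article.** 80 patients allocated 1:1, hence 40 per arm (2.1); a binary sign (2.4); three types at month 12 (3.1); alpha 0.05 (3.3), taken as two-sided. The article gives no prevalence, rate or power figure for this endpoint, so there is nothing to reproduce.

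**Assumptions, none from the article.** Baseline prevalence p = 20%, 40% or 60%; disappearance r among baseline-positive patients; new onset i = 5% among baseline-negative patients.

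**Step 1. Where each patient falls.**

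| Baseline | Month 12 | Type |
|---|---|---|
| absent | absent | A |
| present | present | A |
| present | absent | B |
| absent | present | C |

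**Step 2. Dependence on prevalence.** A = (1−p)(1−i) + p(1−r); B = p·r; C = (1−p)·i. With r = 40% and i = 5%:

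- p = 20%: A = 0.76 + 0.12 = 88%, B = 8%, C = 4%. Of type A, 0.76/0.88 = 86% never had the sign.
- p = 40%: A = 0.57 + 0.24 = 81%, B = 16%, C = 3%. Never present: 70% of A.
- p = 60%: A = 0.38 + 0.36 = 74%, B = 24%, C = 2%. Never present: 51% of A.

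**Step 3. Dilution.** Suppose disappearance is truly 70% versus 30% among patients at risk, a difference of 40 points. At p = 40%, type B over all patients is 0.4 × 0.7 = 28% versus 0.4 × 0.3 = 12%, a difference of 16 points. At p = 20% it is 14% versus 6%, or 8 points.

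**Step 4. Power.** I simulated 200,000 trials per scenario with 40 per arm, disappearance 70% versus 30%, and new onset 5% in both arms. The comparator is a Mantel-Haenszel test of presence at month 12, stratified by baseline presence, without continuity correction.

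| Baseline prevalence | Chi-squared on A/B/C | Mantel-Haenszel | Gain (points) |
|---|---|---|---|
| 20% | 15.5% | 22.1% | 6.6 |
| 40% | 35.1% | 51.5% | 16.4 |
| 60% | 58.0% | 75.3% | 17.3 |

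Shorter runs gave 15%, 35% and 59% against 22%, 51% and 77%, so I quote the gain as roughly 7 to 18 points. With a continuity correction the Mantel-Haenszel power falls to 11.7%, 38.6% and 65.6%. The gain then shrinks, and at 20% prevalence it reverses.

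**Step 5. Type I error.** With no drug effect (r = 40% or 60% in both arms, p = 20 to 60%), the three-type chi-squared rejects in about 3 to 4% of trials. The uncorrected Mantel-Haenszel test rejects in about 5%.

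**Step 6. Chance imbalance.** By exact binomial calculation with 40 per arm, prevalence differs by at least 10 points in 33% of trials at p = 20% and 42% at p = 40%. It differs by at least 20 points in 3.5% and 8.6%. Given a baseline split of 20/40 versus 12/40 and no drug effect, with r = 40%, the expected A/B/C shares are 77.5/20.0/2.5% versus 84.5/12.0/3.5%. The three-type test then rejects in about 8% of trials at r = 40% and 10 to 11% at r = 60%. The stratified test stays at about 5%.

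**The case against.** The tempting stronger reading is that the arms can differ on this endpoint with no drug effect, so that the endpoint yields false positives. The article does not support that. Allocation is randomised, so baseline prevalence is equal in expectation, and the nominal alpha already covers chance imbalance (step 5). The excess in step 6 applies only after an unlucky draw.

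A second tempting reading is that the merging in type A causes the dependence on prevalence. It does not: B = p·r and C = (1−p)·i vary with p whether or not A is split. A fourth category alone would cure only the labelling.

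A third objection is that the article names its tests as examples and never commits in so many words to a three-by-two test over all randomised patients. Denominators and covariates commonly belong to an analysis plan, which is not shown and may set them. This stands as far as it goes, and missing detail is not the charge. But the three-type classification is stated here as a primary endpoint, and a plan that follows it inherits the pooled category.

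It is also true that persistent cases can be recovered as baseline positives minus type B, since every patient is scanned at baseline and month 12. That shows the remedy is cheap; it does not make the three-type comparison readable. Finally, the power gain rests on a large assumed effect and on a test without continuity correction.

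**Conclusion.** The point holds as one of interpretability and efficiency, not of bias. As defined, the endpoint pools two opposite plaque states, and its between-arm comparison has no direction. It is diluted by patients not at risk and is sensitive to a chance baseline imbalance. Under the assumed rates it gives up roughly 7 to 18 points of power against a stratified test. Overall type I error is preserved at about 3 to 4%.

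The definition and the absence of baseline status from the stated comparison come from the article itself. The sizes depend wholly on assumed prevalence and rates, and on new onset being the same in both arms. This is one of seven listed primary endpoints, so it deserves correction before comparative data are seen, but it does not undermine the trial as a whole.

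**What to change.** 1. Make the between-arm test for endpoint 6 the presence of T1 hyperintensity at month 12, stratified by baseline presence (Mantel-Haenszel) or adjusted for it by logistic regression (Firth or exact if counts are sparse). This gives one effect with a clear direction: fewer patients with the sign is better.
2. State whether a continuity correction applies. The gain shown was computed without one, and conservative versions give part or all of it back.
3. Report type B out of baseline-positive patients and type C out of baseline-negative patients, by arm.
4. Show type A as two rows, absent/absent and present/present, and tabulate baseline presence by arm.

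The cost is a few sentences in the endpoint definition and the analysis plan, fixed before comparative data are seen. Baseline T1 hyperintensity is already part of the planned image reading, so no new scan, reading or patient is needed.
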